## Abstract

**Background:**

Ankle fracture fixation surgery may be performed with or without the use of a tourniquet. Surgeons who use a tourniquet report reduced intraoperative bleeding, which improves the visualisation of anatomical structures. This may facilitate more accurate fracture fixation and restoration of the anatomical configuration of the ankle joint, potentially leading to improved functional outcomes. An additional proposed benefit of tourniquet use is reduced operative time. In contrast, surgeons who choose not to use a tourniquet report concerns that it may exacerbate postoperative pain and increase the risk of venous thromboembolism, surgical site infection and other complications. However, existing clinical trials are limited by small sample sizes and high risk of bias, preventing the ability to draw robust conclusions. This study aimed to assess the feasibility of conducting a randomised controlled trial (RCT) to evaluate the potential benefits and risks of tourniquet use in ankle fracture fixation surgery.

**Methods:**

This study comprises a two-centre, participant-blinded and surgeon-blinded parallel-arm RCT and an integrated qualitative interview study. A computer-generated randomisation service will allocate up to 50 patients to undergo ankle fracture fixation surgery either with or without the use of a tourniquet. Participants will be followed up for 3 months postoperatively. Primary outcomes include recruitment and retention rates, data completeness, success of blinding and adherence to allocated intervention. Secondary outcomes include postoperative pain, quality of the surgical field, intraoperative blood loss, blood transfusions, procedure duration, skin assessment, awareness of tourniquet use, health-related quality of life (EuroQol-5D-5L), Olerud-Molander Ankle Score and intraoperative and postoperative complications. The integrated qualitative study will consist of semistructured interviews with up to 12 patients and 12 trauma and orthopaedic surgeons (~24 interviews). Interviews will explore perspectives on the feasibility trial, identify factors associated with unblinding and examine barriers and potential solutions to the design and delivery of a future definitive trial. Interviews will be analysed using inductive thematic analysis.

**Ethics and dissemination:**

National Research Ethics Committee (East of England-Essex) approved this study on the 8 May 2025 (REC 25/EE/0051). The results will be disseminated via peer-reviewed publication.

**Trial registration number:**

ISRCTN91783787.

STRENGTHS AND LIMITATIONS OF THIS STUDYComprehensive feasibility research.Multicentre design.Blinding of patients and surgeons (delivering intervention).Small sample size.Follow-up is limited to 3 months postoperatively.

## Introduction

 Ankle fractures account for approximately 10% of all fractures sustained,^1 2^ with around half of affected patients requiring open reduction internal fixation (ORIF) surgery to restore the anatomical alignment of the ankle joint using various implants. Despite surgical intervention, a substantial proportion of patients report persistent functional limitations, and many are unable to return to their preinjury levels of activity.^3^,^5^ Moreover, complication rates following ORIF for ankle fractures are among the highest in trauma and orthopaedic surgery, with approximately 30% of patients experiencing wound complications, surgical site infection, reoperation, chronic pain or complex regional pain syndrome.^6 7^

Ankle fracture fixation surgery may be performed with or without the use of a tourniquet. This is a cuff device typically placed around the patient’s thigh or calf and then inflated throughout the operation to occlude blood flow to and from the lower leg. According to a 2020 survey of trauma and orthopaedic surgeons, the most commonly cited reasons for tourniquet use are to reduce intraoperative blood loss and improve the visualisation of anatomical structures.^8^ Anecdotally, it is also believed that tourniquet use may facilitate the procedure to be performed more quickly with greater ease and accuracy for fracture fixation and restoration of the anatomical configuration of the ankle joint.^9^ This may optimise patients’ functional recovery and reduce their risk of developing post-traumatic ankle osteoarthritis.^10^ In contrast, some surgeons choose to avoid using a tourniquet, citing concerns that the high pressures exerted on the operative limb may increase patients’ pain both intraoperatively and postoperatively.^11^,^13^ In addition, tourniquet use may increase the risk of venous thromboembolism as a result of arterial and venous stasis. The resulting prolonged ischaemia to the soft tissues, which are already compromised by the initial traumatic injury, can lead to further tissue damage and inflammation, potentially impairing wound healing and increasing the risks of wound-related complications and surgical site infection.^13^,^16^

Although tourniquet use may potentially improve functional outcomes, it may also increase the risk of complications. Previous systematic reviews and meta-analyses of randomised controlled trials (RCTs) have identified up to four tourniquet studies. Across these reviews, the authors reported that definitive conclusions could not be drawn due to small sample sizes and high risk of bias.^12 17 18^ These trials did not evaluate relevant patient-reported (eg, pain intensity, pain character, health-related quality of life (HRQoL) and function) or clinical (eg, analgesia consumption, intraoperative blood loss and quality of the surgical field) outcomes. Review authors recommended further high-quality trials to address this evidence gap. Given the persistent clinical uncertainty surrounding the benefits and risks of tourniquet use in ankle fracture fixation surgery, there is a need for a well-designed multicentre trial addressing the limitations of prior studies and providing robust evidence to inform clinical practice. However, there are several methodological uncertainties that require consideration, including the feasibility of effectively blinding both surgeons and patients to tourniquet use and patient willingness to participate in a clinical trial. Also, many surgeons may be reluctant to alter their established clinical practice for the purposes of research, as views on tourniquet use are ingrained.^8^ Furthermore, the required sample size for a future definitive trial is unknown. Thus, a feasibility trial would evaluate these challenges and determine whether a full definitive trial would be achievable.

We designed a feasibility study comprising two complementary components: a two-centre feasibility RCT, with an integrated qualitative interview study involving patients and surgeons. The study flow diagram is illustrated in figure 1. The qualitative component is intended to contextualise and enhance the interpretation of the feasibility RCT findings by exploring trial processes in depth, including the perspectives of both patients and surgeons. Together, findings from the RCT and qualitative interviews will inform the design, acceptability and feasibility of the future definitive multicentre RCT.

**Figure 1 F1:**
[figure not shown]
Flow diagram illustrating participant progression through the feasibility randomised controlled trial (RCT) and qualitative interview study. Pre-op, Pre-operatively; Post-op, Post-operatively; QIS, qualitative interview study.

The aim of this study was to assess the feasibility of conducting a participant-blinded and surgeon-blinded RCT to evaluate the potential benefits and risks of tourniquet use in ankle fracture fixation surgery.

## Methods

### Feasibility RCT

#### Objectives

Evaluate the willingness of surgeons to recruit participants.Evaluate the willingness of patients to be randomised.Determine reasons for exclusion of patients.Evaluate the feasibility of blinding surgeons to tourniquet status.Evaluate the feasibility of blinding patients to tourniquet status.Evaluate adherence to trial protocol.Estimate key trial parameters and obtain estimates (of clinical and patient-reported outcome measures) to inform sample size calculation.Determine data completeness, withdrawal rates and optimum time points for follow-up.

#### Reporting

This protocol has been developed in accordance with the Standard Protocol Items: Recommendations for Interventional Trials (SPIRIT) guidelines (online supplemental table 1).^19^ The trial will be reported in line with the Consolidated Standards of Reporting Trials (CONSORT) statement.^20^

Online supplemental table 1 summarises the study design and methods in accordance with the WHO Trial Registration Data Set. The current protocol, V.5.2, was approved on 4 December 2025.

#### Study design and eligibility criteria

This is a multicentre, two-arm, parallel-group feasibility RCT. All patients under the care of trauma and orthopaedic consultants at University Hospitals Coventry and Warwickshire (UHCW) and Barts Health National Health Service (NHS) trusts will be eligible for inclusion, provided they meet the criteria outlined in table 1.

**Table 1 T1:** Trial eligibility criteria

Inclusion criteria	Exclusion criteria
Aged 18 years and over. Patients undergoing primary fracture fixation surgery for a closed ankle fracture within 2 weeks of the date of injury under general and/or regional anaesthetic*. Capacity to give informed consent.	Patients with a pilon fracture rather than an ankle fracture. Unable to understand and speak English. Patients with a chronic musculoskeletal or neurological condition (excluding diabetes mellitus) affecting the operative limb or a history of prior surgery on the affected limb, except for temporary external fixation or manipulation under anaesthetic.

* The requirement for surgery within 2 weeks of injury applied only to participants recruited under protocol versions earlier than V.5.1 (1 December 2025). This restriction was removed following a protocol amendment, which was approved by the sponsor and the Research Ethics Committee before implementation.

#### Participant identification, recruitment and consent

Eligible patients will be approached by a member of the research team either in person or remotely (via telephone or video call) to discuss the study before surgery. Patients will be given a participant information sheet and consent form, along with the opportunity to ask questions. Contact details for the research team will be given to participants. Trial recruitment requires signed written consent.

#### Sample size

No formal sample size calculation is required for a feasibility study. Up to 50 participants will be randomised, similar to other feasibility trials.^21^

Recruitment commenced on 19 June 2025 at UHCW NHS Trust and on 15 August 2025 at Barts Health NHS Trust and concluded on 28 February 2026. Follow-up is expected to be completed in May 2026.

To improve participant recruitment, enrolment will take place across two sites, with systematic identification of eligible patients from admission, clinic and operating lists to minimise missed opportunities. Screening logs will be used to track eligibility and reasons for non-participation, with regular review of recruitment rates and site feedback.

#### Interventions and blinding procedure

Participants will receive anaesthesia in accordance with the standard clinical practice of the attending anaesthetist. Once the participant is fully anaesthetised, one inflatable tourniquet cuff will be applied to either the thigh or calf of the operative limb. This tourniquet will be placed over a thin layer of padding and appropriate isolation measures will be used to prevent skin preparation fluids from seeping beneath the tourniquet cuff, in line with the British Orthopaedic Association Standards for Trauma (BOAST) guidance.^22^

To facilitate blinding, all participants will then have a second inflatable tourniquet cuff applied around a standard hospital pillow, positioned on the floor beneath the operating table and concealed with a standard surgical drape. Application of both these tourniquets will be performed by an appropriately trained individual. Each tourniquet cuff will be connected to a pneumatic tourniquet machine (figure 2), with the machine’s controls and display fully concealed from both the operating surgeons and the participant using standard surgical drapes. Exsanguination of the limb may be achieved by elevating it prior to inflation of the tourniquet.

**Figure 2 F2:**
[figure not shown]
Illustration of participant positioning in theatre. While both tourniquet cuffs are connected to the pneumatic tourniquet machine, only the cuff corresponding to the allocated intervention group will be inflated. Group A, surgery with a tourniquet; Group B, surgery without a tourniquet.

At the end of the procedure, once the wound has been closed, dressings applied and any backslab or other support applied, the surgeons will be asked to leave the operating theatre and will not be permitted to return until the tourniquet apparatus has been removed by the remaining theatre team. This measure aims to ensure that surgeons are not able to identify any potential marks of tourniquet use on the limb. Surgeons will be informed of the total duration and pressure settings of tourniquet inflation; however, they will not be informed which tourniquet (limb or pillow) was inflated during the operation.

Adherence to delivery of the allocated intervention will be supported through training at the site initiation visit and dedicated intervention training. Concomitant perioperative and postoperative care is permitted as per local standard practice. No prespecified criteria for modification or discontinuation of the interventions were defined. Any intraoperative discontinuation on safety grounds is managed as part of usual clinical care and documented as a deviation.

Unblinding will only be permitted in a clinical emergency where knowledge of the allocated intervention is required to guide emergency clinical care. In that event, the allocation will be revealed by opening the participant’s sealed code-breaking envelope, with completion of an unblinding form and notification of the study team.

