#### Clinical outcomes and time points

As this is a feasibility study, the primary outcomes include recruitment and retention rates, data completeness for clinical and patient-reported outcomes, success of blinding and adherence to allocated intervention. Clinical and patient-reported outcomes are not statistically powered and will be summarised descriptively to inform the decision on progression to a future definitive trial.

The secondary outcomes below are also exploratory and not statistically powered. These are intended to inform the selection of outcomes and required sample size for any future definitive trial. They will also provide information on the feasibility of outcome data collection, including questionnaire acceptability and data completeness over follow-up. Participants will receive reminders via phone and/or email to complete outcome questionnaires.

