Postoperative pain will be assessed at multiple time points, evaluating various attributes, including duration, intensity, location and pain characteristics (eg, neuropathic and nociceptive). Pain location and character will be measured at baseline (preoperatively), 24 hours and 3 months postoperatively using the painDETECT questionnaire.^24^ Pain intensity at the ankle, calf and thigh regions will be assessed using an 11-point Numerical Rating Scale, where 0 represents ‘no pain’ and 10 represents ‘worst possible pain’,^25^ at 24 hours, 3 weeks and 3 months postoperatively. Total inpatient analgesic consumption and medications prescribed or recommended at discharge will be recorded. Data on analgesia use (drug name, dosage, route and timing) will be collected for 3 weeks from surgery.Surgeon-reported quality of the surgical field will be evaluated using a 5-point Likert scale (‘very dissatisfied’, ‘dissatisfied’, ‘unsure’, ‘satisfied’ and ‘very satisfied’).Intraoperative blood loss will be quantified by calculating the difference in weight of the surgical swabs before the skin incision and after wound closure, reported in grams. The volume of fluid collected in the suction container will also be measured. To calculate the volume of blood loss, the volume of any irrigation or other fluids used during the procedure will be subtracted, with the final value reported in millilitres.The number of blood transfusions administered intraoperatively and postoperatively until discharge will be recorded, based on hospital records and reported as the number of units transfused.Intraoperative complications, including vascular, ligamentous, tendinous and neurological injuries, will be captured via a surgeon-completed questionnaire.Postoperative complications will be captured using a self-reported questionnaire, sent to participants at 3 months postoperatively (via email or post). This will include wound complications, surgical site infections, deep vein thrombosis, pulmonary embolism and reoperation (planned and unplanned). Responses will be cross-checked with hospital records, which will also be reviewed to identify additional complications such as fracture non-union, mal-union and neurovascular injury.Tourniquet-related skin injuries, including burns, contusions and pressure sores, will be assessed based on clinical documentation from the operating department practitioners who routinely inspect the tourniquet site before and after its use.Awareness of tourniquet use will be assessed by asking participants and surgeons to complete a short questionnaire on the day of surgery and at 3 months (eg, ‘*Do you think a tourniquet was used during the operation?’*).Procedure duration will be recorded in minutes, from the time of skin incision to completion of wound closure for the ankle fracture fixation procedure.The Olerud-Molander Ankle Score is a validated 9-item patient-reported outcome measure used to assess functional recovery after ankle injuries.^26^ It assesses pain, functional activities and symptoms such as stiffness and swelling, with a total score ranging from 0 to 100 (higher scores indicate better outcomes).HRQoL will be assessed using the EuroQol-5D-5L questionnaire, a self-completed instrument comprising a five-dimensional health status classification system and a visual analogue scale.^27^

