
Table 2 details the time points at which each outcome will be assessed.

**Table 2 T2:** Time points for assessment of outcomes

Timing	Baseline (retrospective pre injury score)	On day of surgery (pre operatively)	On day of surgery (post operatively)	24 hours post operatively	2 weeks post operatively	3 weeks post operatively	3 months post operatively
Outcome							
Pain (painDETECT)	✓			✓			✓
Pain (NRS)				✓		✓	✓
Analgesia use	✓		✓			✓	
Surgical field of view			✓				
Blood loss			✓				
Blood transfusions			✓		✓		
Length of procedure			✓				
Skin assessment		✓	✓				
Awareness of tourniquet use			✓				✓
EQ-5D-5L	✓					✓	✓
OMAS	✓					✓	✓
Intraoperative complications			✓				
Postoperative complications							✓

EQ-5D-5L, EuroQol-5D-5L; NRS, Numerical Rating Scale; OMAS, Olerud-Molander Ankle Score .

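### Surgeons may return once the cuff is off, when any marks are exposed, and nothing places their blinding guess before that return

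*Protocol article*

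**What the plan says.** All references are to the protocol article.

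- **Cuff on every limb** (Interventions and blinding procedure): for all participants, "one inflatable tourniquet cuff will be applied to either the thigh or calf of the operative limb", over padding. A second cuff goes round a pillow. Only the cuff that matches the allocation is inflated, so the limb cuff is inflated in Group A and not in Group B.
- **When surgeons leave** (same section, text after Figure 2): "once the wound has been closed, dressings applied and any backslab or other support applied, the surgeons will be asked to leave the operating theatre". The limb cuff is still in place at this point.
- **When they may come back** (same place): they "will not be permitted to return until the tourniquet apparatus has been removed by the remaining theatre team".
- **Why** (same place): "This measure aims to ensure that surgeons are not able to identify any potential marks of tourniquet use on the limb".
- **When the guess is taken** (Clinical outcomes and time points): awareness is measured by "asking participants and surgeons to complete a short questionnaire on the day of surgery and at 3 months". Table 2 places the first of these in the post-operative column for the day of surgery.
- **Status of the outcome** (same section): "the primary outcomes include recruitment and retention rates, data completeness for clinical and patient-reported outcomes, success of blinding and adherence to allocated intervention". The Objectives also list surgeon blinding as a feasibility question in its own right.

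**The concern.** The exclusion ends at the wrong event for its purpose. Skin under a cuff cannot be inspected while the cuff is on; it can be once the cuff is off. The rule keeps surgeons from watching the removal, but not from seeing what the removal uncovers.

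This matters because of what the surgeon's guess is meant to measure. Cues during the operation, bleeding above all, are a genuine test of whether a surgeon can be blinded while fixing an ankle. Marks seen afterwards are a different cue, and a simple change of order would remove it. If a guess is made after seeing the limb, the two cues are combined in one answer, and the primary blinding result cannot say which of them gave the allocation away. The definitive trial would then be designed on a blinding estimate that partly reflects when a form was filled in.

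**Working it through.** The article gives no figure to reproduce here, so the check is mainly one of sequence.

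**1. Order of events as printed**

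| Step | Cuff site | Surgeons |
|---|---|---|
| Closure, dressing, any backslab | Under the cuff | Present |
| Surgeons sent out | Under the cuff | Out |
| Apparatus removed | Exposed | Out |
| Exclusion ends | No covering stated | May return |
| Awareness form, same day | Not stated | Before or after return, not stated |
| Awareness form, 3 months | Not applicable | Always after any return |

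Operating department practitioners also inspect the tourniquet site after use (Clinical outcomes and time points; skin assessment in Table 2). The site is therefore uncovered for a time on the day of surgery. The article does not say whether this falls before or after surgeons come back.

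**2. Illustration A: the site is seen and read correctly in a share f of all operations**

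Assumptions, none of them from the documents: otherwise random guessing, independent guesses, one guess per operation.

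Expected proportion correct = (1 − f) × 0.5 + f × 1 = 0.5 + f/2.

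The article plans "Up to 50 participants will be randomised, similar to other feasibility trials", so take 50 guesses. For a yardstick, use 33 or more correct, the smallest count whose chance under pure guessing is at most 2.5%. This is not a protocol criterion.

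| f | Expected correct | Chance of at least 33 of 50 |
|---|---|---|
| 0 | 50% | 1.6% |
| 10% | 55% | 7.7% |
| 20% | 60% | 23.7% |
| 30% | 65% | 50.6% |
| 50% | 75% | 94.5% |

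**3. Illustration B: marks are noticed on a share q of Group A limbs only**

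The range q = 0.2 to 0.6 is assumed.

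- If unmarked limbs lead to coin-flip guesses, Group A correct = q + (1 − q)/2. The overall figure is the mean of that and 0.5, which is 0.5 + q/4. For q = 0.2, 0.4 and 0.6 this gives 55%, 60% and 65%.
- If absence of marks is always read as no tourniquet, overall correct = (q + 1)/2, giving 60%, 70% and 80%.

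**4. Dependence on the baseline**

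If intra-operative cues alone give a proportion b correct, illustration A becomes b + f(1 − b). The added part is f(1 − b). It equals f/2 at b = 0.5 and shrinks as b rises. Since bleeding is itself a cue, b may well exceed 0.5, and the table in step 2 then overstates the added part.

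**5. Precision**

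The 95% half-width at a proportion of 0.5 is 1.96 × √(0.25/50) = 0.139 for all 50 guesses and 1.96 × √(0.25/25) = 0.196 for an arm of 25. A shift of 5 to 10 points lies within that noise, so the data would not reveal the leak unless the timing of each guess is recorded.

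**The case against.** The strongest reply has four parts.

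- **Return is permitted, not required.** The rule sets an earliest time. Surgeons leave with the dressing and any backslab already on, and the article describes no remaining task for them in theatre. This stands: how often a surgeon comes back to an uncovered limb is unknown. A reader might infer that the measure can never work, or that surgeons will see marks. The text supports neither.
- **Marks may not identify the arm.** A padded cuff is on the limb in both groups, and the article does not say how distinct or lasting marks are. This also stands, and it limits the size. It does not remove the point, because the article itself treats marks as something surgeons should not see.
- **The article is condensed.** Covering the site or timing the form may be settled in the full protocol (V.5.2, not shown) or in site training. That is a fair answer to a complaint about silence. It does not answer the printed rule, which names the event that ends the exclusion and then an aim that this event does not serve.
- **A feasibility trial should detect leaks.** The outcome is success of blinding, not intra-operative blinding alone, and the interviews explore why surgeons were unblinded. This stands in part. The interviews could bring marks to light, but with about 12 surgeons, including some who declined to take part, they cannot sort individual guesses by cue. A reader might infer that the trial will wrongly conclude that surgeons cannot be blinded during fixation. That would require those interview data to be ignored, and the documents do not show it.

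**Conclusion.** The point holds in a limited form. The exclusion ends when any marks become visible, so the rule as printed does not secure its own aim. With the day-of-surgery guess not tied to re-entry, an avoidable post-operative cue can enter a primary feasibility outcome.

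The size cannot be derived from the documents. The percentages above rest on assumed noticing rates, random guessing otherwise and, in illustration B's upper range, surgeons treating absence of marks as conclusive. They show that a modest leak could matter with 50 guesses; they do not estimate the leak. In particular, 60% to 80% correct should not be read as a forecast. The article prints no threshold for successful blinding, so no decision is shown to change.

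The repair is nearly free and separates two cues that mean different things for the definitive trial.

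**What to change.** **If operations are still taking place**, amend the end-of-procedure paragraph under Interventions and blinding procedure so that:

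1. surgeons complete the day-of-surgery awareness form after leaving theatre and before any return;
2. they return only once the cuff site is covered or the form has been recorded;
3. the form notes whether the uncovered cuff site was seen before answering.

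The cost is about one sentence and one tick-box. The downside is that the form is completed slightly earlier. Recording the form first protects only the same-day guess, and covering the site also helps protect the 3-month one.

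**If recruitment has closed**, this cannot help participants already operated on. The article is inconsistent here: Sample size says recruitment concluded on 28 February 2026, while Trial progress says it is still under way. The two statements need reconciling. In that case:

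- report surgeon guesses by whether they were made before or after re-entry, where known;
- report the 3-month guess separately;
- ask about marks in the surgeon interviews;
- state unknown timing as a limitation;
- carry the repaired order into the definitive trial.

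This costs a few lines of reporting and one interview question.
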